###### Depression-Setswana

CES-D: Mo tse di latelang, tlhopa e e tsamaisanang le ka mokgwa o o neng o ikutlwa ka ona mo bekeng e e fitileng

| **CES-D** | | | | |
| --- | --- | --- | --- | --- |
|  | Go se kalo(<1day) | Go le gonnye(1-2 days) | Go le gontsi (3-4 days) | Go le gontsi thata (5-7 days) |
| a. Ke tshwentse ke dilo tse gantsi di sa tshwenyeng | 1 | 2 | 3 | 4 |
| b. Ke bile le bothata ba go tsepamisa tlhaloganyo ya me mo se ke neng ke se dira | 1 | 2 | 3 | 4 |
| c. Ke utlwile dilo tse tsotlhe tse ne ke dira e le matsapa | 1 | 2 | 3 | 4 |
| d. Maikutlo a me a ne a ya ko tlase | 1 | 2 | 3 | 4 |
| e. Ke ikutlwile ke ba le tshepo ka bokamoso | 1 | 2 | 3 | 4 |
| f. Ke ikutlwile ke boifa | 1 | 2 | 3 | 4 |
| g. Ke ne ke tlhobaelwa | 1 | 2 | 3 | 4 |
| h. Ke ne ke thabile | 1 | 2 | 3 | 4 |
| i. Ke ikutlwile ke le bodutu | 1 | 2 | 3 | 4 |
| j. Ke ne ka palelwa ke go tswelela | 1 | 2 | 3 | 4 |

###### Sexual Behaviour-Setswana

| **Sexual behaviour** | | | | | | |
| --- | --- | --- | --- | --- | --- | --- |
| Nagana sentle ka ga dikgwedi tse 3 tse di fitileng mme o tlhophe karabo ya gago. | | | | | | |
| 1. O ne wa tsena mo thobalanong mo kgweding tse tharo tse di fitileng? | Ee [ ] | Nya [ ] | Ga o re nya, e ya ko potso ya bolesome | | | |
| 2. O robalane le borre ba le bakae mo kgweding tse tharo tse di fitileng? | 0 | 1 | 2 | 3 | 4 | 5 kgotsa ba go feta |
| 3. O robalane le bomme ba le bakae mo kgweding tse tharo tse di fitileng? | 0 | 1 | 2 | 3 | 4 | 5 kgotsa ba go feta |

Jaanong nagana sentle ka ga dikgwedi tse 3 tse di fitileng.

Mo kgweding tse 3 tse di fitileng-Ke makgetho a le makae……

| 4. O tsene mo thobalanong ka ntle le go dirisa kgotlhopo? | 0 | 1-2 | 3-5 | 6-10 | 11-20 | 21-30 | 31-40 | 41 kgotsa ba go feta |
| --- | --- | --- | --- | --- | --- | --- | --- | --- |
| 5. O tsene mo thobalanong o dirisa kgotlhopo? | 0 | 1-2 | 3-5 | 6-10 | 11-20 | 21-30 | 31-40 | 41 kgotsa ba go feta |
| 6. O tsene mo thobalanong o nwele bojalwa? | 0 | 1-2 | 3-5 | 6-10 | 11-20 | 21-30 | 31-40 | 41 kgotsa ba go feta |
| 7. Molekane wa gago a nwele bojalwa pele le robalana? | 0 | 1-2 | 3-5 | 6-10 | 11-20 | 21-30 | 31-40 | 41 kgotsa ba go feta |
| 8. O dirisitse diritibatsi pele ga thobalano? | 0 | 1-2 | 3-5 | 6-10 | 11-20 | 21-30 | 31-40 | 41 kgotsa ba go feta |
| 9. Molekane wa gago a dirisitse diritibatsi pele ga thobalano? | 0 | 1-2 | 3-5 | 6-10 | 11-20 | 21-30 | 31-40 | 41 kgotsa ba go feta |

| 10. O ne wa se dirise kgolhopo le molekane yo o sa itseng maemo a gagwe a HIV | [ ] 1. Ee [ ] 2. Nya |
| --- | --- |
| **11. Mo kgweding tse 3 tse di fitileng –Ke itsisitse** Molekane wa bofelo o ke neng ka tsena mo thobalanong le ena ka maemo a me a HIV | [ ] 1. Ee [ ] 2. Nya |

###### Internalized AIDS stigma-Setswana

| **Internalised stigma** | | | | |
| --- | --- | --- | --- | --- |
|  | Go dumela mo go feteletseng | Go dumela | Go se dumele | Go se dumele mo go feteletseng |
| 1. Go boima go bolelela batho ba bangwe ka maemo a ka a HIV | [ ] 1. | [ ] 2. | [ ] 3. | [ ] 4. |
| 2. Ke swabisa ke gore ke HIV+ | [ ] 1. | [ ] 2. | [ ] 3. | [ ] 4. |
| 3. Ka nako tse dingwe ke ikutlwa ke se na boleng ka gonne ke le HIV+ | [ ] 1. | [ ] 2. | [ ] 3. | [ ] 4. |
| 4. Ke ikutlwa ke molato ka go ba HIV+ | [ ] 1. | [ ] 2. | [ ] 3. | [ ] 4. |
| 5. Ke fitlha maemo a me a HIV go ba bangwe | [ ] 1. | [ ] 2. | [ ] 3. | [ ] 4. |
| 6. Go ba HIV+ go dira gore ke ikutlwe ke le maswe | [ ] 1. | [ ] 2. | [ ] 3. | [ ] 4. |
| 7. Ke molato wa me ga ke le HIV+ | [ ] 1. | [ ] 2. | [ ] 3. | [ ] 4. |

####

#### Alcohol consumption-SeTswana

| **The Alcohol Use Disorders Identification Test (AUDIT):**  **Interview Version- Tswana** | | | | | | |
| --- | --- | --- | --- | --- | --- | --- |
| Molwetsi yo o rategang,  Jaana ka e nngwe ya ditsela tseo ke di dirisang go tlhatlhoba maemo a mathata a tsamaisanang le tsa pholo mo botshelong jwa gago. Kitso eo ke tla e fitlhelang e botlhokwa ka gore e tla nthusa go neelana ka thuso kana go oka le tlhokomelo e e kwa godimo. Gore ke kgone go dira seno, ke tla kopa gore o orabe dipotso tse di latelang ka tiriso ya nnotagi mo dikgweding tse thataro tse di fetileng. Dikarabo tsa dipotso tseo di tla beng di boditswe di tla nna mo sephiring. Mo pampiring ya dipotso ga go kitla go ntshiwa sepe se se amanang le leina la gago.  **Age:** ____ Dingwaga **Gender:** [1] Monna [2] Mosadi **Letlha*:*** ____/ ____/ _______  Nnotagi e e lekaneng e: | | | | | | |
| *[figure not shown]* | *Thoto e le nngwe ya sepiriti (whisky, gin & vodka) (e.g., 25ml at 43%)* | *[figure not shown]* | *Galase e le nngwe ya lekaraese*  *(e.g., 25ml at 30%)* | | | |
| *[figure not shown]* | *Khene e le nngwe ya bojalwa*  *(e.g., 340ml at 5%)* | *[figure not shown]* | *Galase e le nngwe ya beine*  *(e.g., 120ml at 12%)* | *[figure not shown]* | *Katone e le nngwe ya bojalwa ba setho*  *(e.g., 500ml at 3%)* | |
| 1. Ke ka makgetlho a le makae o ne o nwa seno se se nang le bojalwa mo dikgweding tse thataro tse di fetileng?  Le goka [*tlolela go Qs 9-10*]……………………….  Kgwedi kana kwa tlase……………………………....  Gabedi go ya go gane mo kgweding……………….  Gabedi go ya go gararo mo bekeng……................  Gane kgotsa go feta mo bekeng…………………. | | (0)  (1)  (2)  (3)  (4)  [__] | 6. Ke ga kae mo dikgweding tse thataro tse di fetileng mo o neng o tlhoka nnotagi fela mosong go tlosa letsapa la nno e ntsi e o nnileng le yone mo bosigong jo bo fetileng?  Le goka...........................................................  Mo tlase ga kgwedi.........................................  Kgwedi nngwe le nngwe.................................  Beke nngwe le nngwe....................................  Tsatsi lengwe le lengwe................................. | | | (0)  (1)  (2)  (3)  (4)  [__] |
| 2. Mo letsatsing ke dinnotagi di le kae tseo o di nwang?  1kgotsa 2…………………………………………….  3kgotsa 4…………………………………………….  5kgotsa 6…………………………………………….  7, 8, kgotsa 9…………………………………………  10 kgotsa go fetisa…………………………………. | | (0)  (1)  (2)  (3)  (4)  [__] | 7. Ke ga kae mo dikgweding tse thataro tse di fetileng nneng wa itshola fa morago ga go nwa nnotagi?  Le goka...........................................................  Mo tlase ga kgwedi.........................................  Kgwedi nngwe le nngwe.................................  Beke nngwe le nngwe....................................  Tsatsi lengwe le lengwe................................. | | | (0)  (1)  (2)  (3)  (4)  [__] |
| 3. Ke ka makgetlho a le kae (fa o le monna) tse tlhano kana go feta le (fa o le mosadi) dinnotagi di le nne kgotsa go feta mo kopanong e le nngwe?  Le goka...................................................................  Mo tlase ga kgwedi.................................................  Kgwedi nngwe le nngwe.........................................  Beke nngwe le nngwe.............................................  Tsatsi lengwe le lengwe..........................................  ***Tlolela ko potsong ya 9 and 10 if Total Score for Qs 2 and 3 is =0*** | | (0)  (1)  (2)  (3)  (4)  [__] | 8. Ke ka makgetlho a makae mo dikgweding tse thataro mo e leng gore o paletswe ke go gopola gore go diragetseng bosigo bo bo fetileng ka gonne o ne o nole?  Le goka..........................................................  Mo tlase ga kgwedi.........................................  Kgwedi nngwe le nngwe.................................  Beke nngwe le nngwe....................................  Tsatsi lengwe le lengwe................................. | | | (0)  (1)  (2)  (3)  (4)  [__] |
| 4. Ke ka makgetlho a le makae mo dikgweding di le thataro tse di fetileng mo o fitlhetseng e le gore fa o simolola go nwa nno-tagi o palelwa ke go emisa?  Le goka...................................................................  Mo tlase ga kgwedi.................................................  Kgwedi nngwe le nngwe.........................................  Beke nngwe le nngwe.............................................  Tsatsi lengwe le lengwe.......................................... | | (0)  (1)  (2)  (3)  (4)  [__] | 9. A go mongwe kgotsa wena o kile wa gobala ka ntlha ya nnotagi?  Nnya ya…………………………………………..  Ee, e seng mo dikgweding tse thatarotse di  fetileng…………………………………………  Ee, Mo dikgweding tsedithataro tse di fetileng | | | (0)  (2)  (4)  [__] |
| 5. Ke ka makgetlho a le makae mo ngwageng o fetileng mo o reteletsweng ke go dira seo o neng o tshwanetse ke go se dira ka ntlha ya nnotagi ya gago?  Le goka...................................................................  Mo tlase ga kgwedi.................................................  Kgwedi nngwe le nngwe.........................................  Beke nngwe le nngwe............................................  Tsatsi lengwe le lengwe......................................... | | (0)  (1)  (2)  (3)  (4)  [__] | 10. A mongwe wa losika kgotsa tsala, ngaka, kgotsa modiredi wa tsa pholo yo o kileng a tshwenyega ka go nwa nnotagi ga gago kgotsa a rotloetsa gore o fokotse bojalwa?  Nnya ya…………………………………………..  Ee, e seng mo dikgweding tse thatarotse di  fetileng…………………………………………  Ee, Mo dikgweding tsedithataro tse di fetileng | | | (0)  (2)  (4)  [__] |
| Rekoto ya ditiriso tse di maleba [____] | | | | | | |

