#### Annex 3: Alcohol consumption

| **The Alcohol Use Disorders Identification Test (AUDIT): Interview Version-English** | | | | | | |
| --- | --- | --- | --- | --- | --- | --- |
| Dear Patient,  As part of my service I am examining lifestyle issues likely to affect the health of my patients. This information is important because it will assist me in giving the best treatment and highest possible standard of care. To help me do this, now I would like to ask you some questions about your use of alcohol beverages during the past 3 months. Your answers to these questions will be treated in strict confidence. No details of your name will be written on this questionnaire.  **Age:** ____ years **Gender:** [1] Male [2] Female **Date*:*** ____/ ____/ _______  A standard drink is: | | | | | | |
| *[figure not shown]* | *A single tot of spirits (whisky, gin & vodka)*  *(e.g., 25ml at 43%)* | *[figure not shown]* | *A small glass of liqueur or aperitif*  *(e.g., 25ml at 30%)* | | | |
| *[figure not shown]* | *1 can of ordinary beer*  *(e.g., 340ml at 5%)* | *[figure not shown]* | *1 glass of wine*  *(e.g., 120ml at 12%)* | *[figure not shown]* | *Cartoon of ordinary commercial sorghum beer*  *(e.g., 500ml at 3%)* | |
| 1. How often do you have a drink containing alcohol in the past 3 months?  Never [*skip to Qs 9-10*]……………………………….  Monthly or less.........................................................  2 to 4 times a month…………………………………..  2 to 3 times a weeks…………………………………..  4 or more times a week...……………………….......... | | (0)  (1)  (2)  (3)  (4)  [___] | 6. How often during the last 3 months have you needed a first drink in the morning to get yourself going after a heavy drinking session?  Never…………………………………………...  Less than monthly……………………………..  Monthly…………………………………………  Weekly……………………………………….....  Daily or almost daily …………………………. | | | (0)  (1)  (2)  (3)  (4)  [___] |
| 2. How many drinks containing alcohol do you have on a typical day when you are drinking?  1 or 2……………………………………..……...……  3 or 4…………………………………………..……...  5 or 6……………………………………………….....  7, 8 or 9………………………………………………...  10 or more……………………………………………... | | (0)  (1)  (2)  (3)  (4)  [___] | 7. How often during the last 3 months have you had a feeling of guilt or remorse after drinking?  Never…………………………………..……….  Less than monthly………………………..……  Monthly…………………………………….......  Weekly……………………………………........  Daily or almost daily………………………..… | | | (0)  (1)  (2)  (3)  (4)  [___] |

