| 3. How often do you have (for men) five or more and (for women) four or more drinks on one occasion?  Never  Less than Monthly  Monthly  Weekly  Daily or almost daily  ***Skip to question 9 and 10 if Total Score for Qs 2 and 3 is =0*** | | (0)  (1)  (2)  (3)  (4)  [___] | 8. How often during the last 3 months have you been unable to remember what happened the night before because you had been drunk?  Never  Less than monthly  Monthly  Weekly  Daily or almost daily | | | (0)  (1)  (2)  (3)  (4)  [___] |
| 4. How often during the last 3 months have you found that you were not able to stop drinking once you had started?  Never……………………………………………………  Less than monthly……………………………………..  Monthly………………………………………………….  Weekly…………………………………………………..  Daily or almost daily…………………………………... | | (0)  (1)  (2)  (3)  (4)  [___] | 9. Have you or someone else been injured as a result of your drinking?  No……………………………………………….  Yes, but not in the last 3 months…………….  Yes, during the last 3 months……………….. | | | (0)  (2)  (4)  [___] |
| 5. How often during the last year have you failed to do what was normally expected from you because of drinking?  Never……………………………………………………  Less than monthly……………………………………..  Monthly………………………………………………….  Weekly…………………………………………………..  Daily or almost daily………………………………… | | (0)  (1)  (2)  (3)  (4)  [___] | 10. Has a relative or friend or a doctor or another health worker been concerned about your drinking or suggested you to cut down?  No……………………………………………….  Yes, but not in the last 6 months…………….  Yes, during the last 6 months……………….. | | | (0)  (2)  (4)  [___] |
| Record total of specific items here [____] | | | | | | |

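### The AUDIT asks about 3 months in English but six months in Setswana, so one score covers different periods by language at screening and at the 3-month visit

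*Protocol*

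**What the plan says.** The Protocol gives the AUDIT at baseline, 3 and 12 months, in English or Tswana (Data collection instruments, Alcohol consumption). The score decides entry, at 8-19 for men and 7-19 for women (Inclusion criteria). It is also the alcohol measure in the 2 x 3 repeated-measures ANOVA (Data Analysis).

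The English form opens with "now I would like to ask you some questions about your use of alcohol beverages during the past 3 months", and item 1 repeats that period: "How often do you have a drink containing alcohol in the past 3 months". Two items depart from it. Item 5 asks "How often during the last year have you failed to do what was normally expected from you because of drinking", and item 10 offers "Yes, but not in the last 6 months" and "Yes, during the last 6 months".

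The Setswana form opens with "ke tla kopa gore o orabe dipotso tse di latelang ka tiriso ya nnotagi mo dikgweding tse thataro tse di fetileng". Its dated items use the same numeral, *thataro*, except item 5, which asks about the past year.

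The Protocol neither mentions nor explains the difference.

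**The concern.** Patients with the same drinking history can score differently because of the interview language alone. That touches two uses of the score.

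- **Screening:** the same cut-offs are applied to answers about different periods.
- **The 3-month outcome:** a six-month window at that visit is half filled with time before the intervention, so a real early change shows only in part. When that earlier time later drops out of the window, the score can fall between 3 and 12 months with no further change in drinking. This bears on the hypothesis that consumption in the intervention group keeps falling over the 12 months.

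An analysis plan cannot recover a period that the form did not ask about separately. Annex 1 records the household language (item 1.2) but shows no field for the language of the interview, so adjusting for language may not be possible either.

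**Working it through.** **1. The numerals, from the Protocol itself.** The Setswana sexual-behaviour form asks "O ne wa tsena mo thobalanong mo kgweding tse tharo tse di fitileng" under a heading that gives the same period with the digit 3, so *tharo* is three. English AUDIT item 10 says 6 months where Setswana item 10 says *thataro*, so *thataro* is six.

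**2. The windows side by side.**

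| AUDIT part | English | Setswana |
|---|---|---|
| Introduction | 3 months | 6 months |
| Items 1, 4, 6, 7, 8, 9 | 3 months | 6 months |
| Item 5 | 1 year | 1 year |
| Item 10 | 6 months | 6 months |
| Items 2, 3 | undated | undated |

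Six of the eight dated items differ by language, as does the introduction that frames the undated items.

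**3. Screening example.** Take a patient whose drinking led to an injury 4 months ago. Item 9 scores 2 in English (yes, but before the window) and 4 in Setswana (within the window). A man with 5 points on the other items totals 5 + 2 = 7 in English (not eligible) and 5 + 4 = 9 in Setswana (eligible). With 17 other points he totals 19 (eligible) or 21 (excluded).

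**4. Outcome example.** Take an injury 1 month before the intervention and none after it. Item 9 scores:

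| Visit | English | Setswana |
|---|---|---|
| Baseline | 4 | 4 |
| 3 months (injury 4 months ago) | 2 | 4 |
| 12 months (injury 13 months ago) | 2 | 2 |

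The same history gives a fall by month 3 in English and a fall between months 3 and 12 in Setswana.

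**5. Reach at the 3-month visit.** A window of w months lies after the intervention for a share min(1, 3/w): 1 for 3 months, 0.5 for 6 months, 0.25 for 12 months. Windows reach before the intervention in 2 of 8 dated English items (5 and 10) and in 8 of 8 Setswana items.

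**6. Illustrative size.** Assumptions, not in the Protocol: answers average evenly over the window, items weigh equally, and the points that items 9 and 10 give for earlier events are ignored. The share of the 3-month change retained is then:

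- English, with items 2 and 3 following the 3-month introduction: (6 x 1 + 0.25 + 0.5 + 2 x 1)/10 = 0.875.
- Setswana, with items 2 and 3 following the six-month introduction: (7 x 0.5 + 0.25 + 2 x 0.5)/10 = 0.475.
- Setswana, with items 2 and 3 answered as current drinking: (7 x 0.5 + 0.25 + 2 x 1)/10 = 0.575.

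The language split is not given. For Setswana shares of 25%, 50% and 75%, the mixture retains 77.5-80%, 67.5-72.5% and 57.5-65%.

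**7. The 12-month visit.** The longest window is one year (item 5), which reaches back only to about the intervention. There is one indirect route: Data Analysis fills a single missing follow-up with the one available, so a 3-month score can stand in for month 12.

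**8. Sample size.** The 251 per group rests on ART adherence, not on AUDIT, and is unaffected.

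**The case against.** The strongest reply is that the damage is narrow and its size unproven. Much of that stands.

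- In English, six of eight dated items have a window equal to the follow-up interval. A reader might infer that the 3-month outcome as a whole counts pre-intervention drinking; that describes the Setswana form, and in English only items 5 and 10.
- A reader might infer bias in favour of one arm. Randomisation should balance language between arms, which leaves dilution and noise.
- A reader might infer that the cut-offs select different drinkers throughout. A steady drinker gives the same frequency answer over 3 or six months. The difference affects patients whose drinking recently changed, or who had an item 9 event between 3 and six months ago.
- It is tempting to count the maximum points of the affected items, or to speak of a total loss. Eligible patients score at most 19 of 40. In items 9 and 10 an earlier event still scores 2, so the window moves each by at most 2 points. Only that step can be lost entirely.
- Items 1, 4 and 6-8 ask for a frequency category, and patients may report current habit. Even averaging is therefore an assumption, and a power loss cannot be derived from the documents.
- Questionnaires are pre-tested before recruitment (Time line and research activity), which might catch the mismatch. Nothing in the Protocol makes that certain.

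None of this explains why the two language forms ask about different periods.

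**Conclusion.** The forms are wrong as written: the same AUDIT score covers different recall periods by language. The consequences are limited to screening and the 3-month visit, plus any 12-month value imputed from month 3.

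The expected effect is a 3-month between-arm difference diluted toward zero, with added noise. In Setswana interviews there may also be an artefactual decline from 3 to 12 months, which matters most for the within-arm hypothesis of continued reduction. The documents do not support a claim of bias toward one arm or of window carry-over in observed 12-month scores.

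The size is unknown. Under even averaging, up to half of the change in the six-month items is lost at 3 months. The whole-score shares above illustrate that assumption and do not estimate the loss. The mismatch itself needs no assumption, and it cannot be repaired once baseline data have been collected.

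**What to change.** Before the pre-test and printing planned for August 2011:

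- Set every dated AUDIT item, including 5, 9 and 10, to the past 3 months in both languages at all three visits.
- Back-translate the Setswana form against the English one.
- Add a field for interview language at each visit.

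The cost is text editing and one back-translation. There are two downsides. The 12-month visit then covers only months 9 to 12, as six of the eight dated English items already do. The 2-point answers of items 9 and 10 still count earlier events in both languages, so some carry-over remains.

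Separately, and minor: the English leaflet (Annex 6) gives a tot of spirits as 52 ml, while both AUDIT forms, the standard-units table and the Setswana leaflets give 25 ml. This looks like a transposed digit and should be reconciled.

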#### Inclusion criteria

-HIV 1 positive male and female patients

-Outpatients

-18 years and above

-No mental impairment

-Medium risk drinkers (i.e. 8-19 for men and 7-19 for women on the AUDIT questionnaire)

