#### Exclusion criteria

-A score of 20 and above on the AUDIT questionnaire

-A score of less than 8 for men and less than 7 for women on the AUDIT questionnaire

-Pregnant patients

-Patients already under alcohol reduction treatment

-Patients with mental impairment

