**Fa osa dumalelane’, e ya kwa letlheng le lengwe**

TOB.2 Mo kgweding e e fetileng, ke ga kae o dirisa e mongwe kgotsa go feta ga mefuta ya metsoko e e latelang (cigarettes, snuff, chewing tobacco, cigars, etc.)?

| Gangwe kgotsa gabedi | 1 |
| --- | --- |
| Beke nngwe le nngwe | 2 |
| Go isa go letsatsi ka letsatsi | 3 |
| Letsatsi lengwe le lengwe | 4 |

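### The English and Setswana AUDIT forms are not equivalent in item 2 and in the top option of items 3 to 8, so interview language can change a patient's eligibility or referral class

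*Protocol*

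**What the plan says.** The protocol prints the AUDIT twice, in English (Annex 3) and in Setswana (Alcohol consumption-SeTswana). The section on alcohol consumption says that questionnaires are given in either language and that the AUDIT is repeated at 3 and 12 months.

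- **Item 2.** English: "How many drinks containing alcohol do you have on a typical day when you are drinking". Setswana: "Mo letsatsing ke dinnotagi di le kae tseo o di nwang".
- **Items 3 to 8, option scored 4.** English: "Daily or almost daily". Setswana, in all six items: "Tsatsi lengwe le lengwe". The option below it, scored 3, is weekly in both forms.
- **Cut-offs.** There is one set for both languages. The inclusion criterion is "Medium risk drinkers (i.e. 8-19 for men and 7-19 for women on the AUDIT questionnaire"; the matching exclusion is "A score of 20 and above on the AUDIT questionnaire", and the Procedure section refers those patients for further management.

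The AUDIT also supplies the prevalence and drinking-pattern figures of the first two objectives and the alcohol use score in the repeated-measures analysis (Data Analysis).

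**The concern.** A translated instrument can share cut-offs with its source only if the same drinking earns the same points. Two wordings break that here. The Setswana item 2 stem contains nothing that limits it to days on which the patient drinks, so it can be heard as a question about any day. In items 3 to 8 the Setswana form offers no option for someone affected on most days but not every day. That person must choose between weekly (3) and every day (4), whereas the English form assigns 4.

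The AUDIT is the gate into the trial, the trigger for referral and the alcohol outcome. If the form's language moves a score across 7, 8 or 20, then who is screened out, who is randomised and who is referred depend partly on the language of interview. A patient wrongly screened out is not followed, so the error cannot be repaired in the analysis.

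**Working it through.** **Step 1. Scale check.** Ten items with a top score of 4 give 10 x 4 = 40, the maximum that the protocol states. The printed codes are the same in both forms; only the wording differs.

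**Step 2. Does the Setswana top option mean every day only?** The tobacco question TOB.2 serves as an internal key, because it lists almost daily (code 3) and daily (code 4) as separate answers. Its Setswana version gives "Go isa go letsatsi ka letsatsi" for code 3 and "Letsatsi lengwe le lengwe" for code 4. The Setswana AUDIT uses nearly the code 4 phrase, "Tsatsi lengwe le lengwe", and the code 3 phrase appears nowhere in it. The reading therefore rests on the protocol's own parallel text.

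**Step 3. Effect of the option wording alone.** For each of items 3 to 8 on which the true frequency is almost daily, English scores 4. Setswana scores 3 if the patient picks the weekly option, a loss of 1 point. With k such items the loss is k, at most 6.

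Constructed example: item 1 = 4, item 2 = 2 in both forms, items 3, 4, 6 and 7 almost daily, all other items 0.
- English: 4 + 2 + (4 x 4) = 22, excluded and referred.
- Setswana: 4 + 2 + (4 x 3) = 18, within 8-19 and 7-19, randomised.

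Item 2 is held equal on purpose, so the 4-point gap comes only from the option wording.

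**Step 4. Effect of item 2, if the patient averages over the week.** This is an assumption about how the question is answered. The bands are 1-2 = 0, 3-4 = 1, 5-6 = 2, 7-9 = 3, 10 or more = 4, with averages rounded to whole drinks.

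| Drinks per drinking day | Days per week | English score | Average per calendar day | Setswana score, averaged |
|---|---|---|---|---|
| 6 | 2 | 2 | 12/7 = 1.7 | 0 |
| 10 | 2 | 4 | 20/7 = 2.9 | 1 |
| 6 | 5 | 2 | 30/7 = 4.3 | 1 |
| 6 | 7 | 2 | 42/7 = 6.0 | 2 |

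A weekend drinker with item 1 = 3, six drinks on two days and item 3 weekly (3) totals 3 + 2 + 3 = 8 in English, eligible for either sex. With averaging the Setswana total is 3 + 0 + 3 = 6, not eligible. A patient who answers for a drinking day, or who drinks every day, scores the same in both forms.

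The skip rule can add to this. Items 4 to 8 are omitted when items 2 and 3 sum to 0. Four drinks on two days a week, with item 3 at never, scores 1 on English item 2. Averaged (8/7 = 1.1), it scores 0 and all five items are skipped.

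**Step 5. An opposing difference.** In the introduction and items 1, 4 and 6 to 9, English asks about three months and Setswana about six (*thataro*, the word that also renders the six months of English item 10; the Setswana sexual behaviour form uses *tharo* for three). Constructed example: item 1 = 2, item 2 = 1, item 3 = 2, an injury four months ago, all other items 0.
- English: item 9 = 2, total 2 + 1 + 2 + 2 = 7.
- Setswana: item 9 = 4, total 2 + 1 + 2 + 4 = 9.

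A man with this history is ineligible on the English form and eligible on the Setswana form.

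**The case against.** **Item 2 may be understood as intended.** Patients who answer never to item 1 skip item 2, and item 2 has no zero option, so in context it presupposes a day with alcohol. Nothing in the stem asks for a weekly average. A man who has eight drinks every Saturday may well say eight. This stands: the item 2 loss is possible but not established, and no independent translation is at hand.

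**The option effect is an upper bound.** Weekly does not describe five or six days a week either, so some patients will round up to every day and lose nothing. The 22 against 18 example is also constructed. A recent expression of concern (item 10 = 4) would give 26 and 22, referred in both languages. This stands as a limit on size. It does not make the options equivalent.

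**Stronger readings that the documents do not support.**
- A reader might infer that the same drinking always scores lower in Setswana. It does not: most answers are unaffected, and the longer recall can push scores up.
- A reader might add 6 points from items 3 to 8 to 4 from item 2 and call 10 the maximum loss. Losing 4 on item 2 by averaging needs about one heavy day a week, while losing 6 on items 3 to 8 needs near-daily problems. At five drinking days a week, ten drinks average 50/7 = 7.1, which scores 3 instead of 4, so averaging costs 1 point and the joint loss is about 7.
- A reader might infer a biased treatment effect. Patients are randomised individually, so the mismatch does not by itself favour an arm, and the sample size does not depend on it.

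**Pre-testing is already planned.** True, and it is the right occasion for the correction. The timeline does not say that the two versions will be compared.

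**Conclusion.** The concern holds in a limited form. The English and Setswana AUDIT forms differ in item 2 and in the 4-point option of items 3 to 8, and the same cut-offs are applied to both.

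The better-supported part is the option wording: up to 1 point on each of six items, for patients who are almost daily on that item and choose the weekly option. That is enough to move a patient from 22 to 18. The item 2 effect needs the further assumption of averaging over non-drinking days. Neither difference fixes a net direction between the forms, because the recall mismatch can work the other way; it adds a second source of non-equivalence.

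What is affected is eligibility, screening prevalence, referral class and the comparability of scores across languages, with added measurement error if a patient changes language between visits. The documents give neither the share of Setswana interviews nor the share of almost-daily answers, so no misclassification rate can be stated.

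**What to change.** Before the questionnaires are printed:

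1. Reword Setswana item 2 so that it refers to a typical day on which the patient drinks.
2. Reword the top option of Setswana items 3 to 8 to every day or almost every day.
3. Reconcile the recall period of the two forms at the same time.
4. Check the changes by back-translation at the pre-test scheduled for August 2011.
5. Record the interview language at each visit and, where possible, keep one language per patient.

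The cut-offs stay as they are. The cost is revised wording in seven items plus the recall phrases, and one field on the form. Pre-testing (R 1,000) and printing (R 6,000) already have budget lines; back-translation is not listed separately and would be a small addition.

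### Setswana AUDIT item 9 leaves out the restriction to the respondent's own drinking, so an injury due to someone else's drinking can add 2 or 4 points to the score that sets eligibility and measures the alcohol outcome

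*Protocol*

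**What the plan says.** The protocol prints the AUDIT in two languages. In the English form (Annex 3: Alcohol consumption) item 9 reads "Have you or someone else been injured as a result of your drinking". In the Setswana form (Alcohol consumption-SeTswana) it reads "A go mongwe kgotsa wena o kile wa gobala ka ntlha ya nnotagi". Both versions score the answers 0, 2 or 4: no, yes but outside the recent window, yes within it.

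Elsewhere the Setswana form does say whose drinking is meant. Item 5 has "ka ntlha ya nnotagi ya gago" and item 10 has "a tshwenyega ka go nwa nnotagi ga gago"; *gago* means 'your' in each.

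The total has three uses:
- It sets entry (Inclusion criteria): "Medium risk drinkers (i.e. 8-19 for men and 7-19 for women on the AUDIT questionnaire".
- It sets exclusion below those limits and at 20 or more (Exclusion criteria), with referral at 20 or more (Procedure).
- It is the alcohol use score compared over the three contact periods (Data Analysis).

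The section on alcohol consumption under Data collection instruments has the AUDIT given at baseline, 3 and 12 months, and all questionnaires given in English or Tswana.

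**The concern.** Items 1 to 8 ask what the respondent did or felt, so the subject of the sentence largely settles whose drinking is scored. Item 9 is different because it deliberately brings in a third party. In English, only the reference to the respondent's drinking keeps the item about the respondent. The Setswana wording does not print it. A patient who was hurt by another drinker can then truthfully answer yes. The same may hold for a patient who knows someone hurt through alcohol.

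Points gained in this way do not measure the patient's own drinking. They can move a patient across either eligibility limit. They also add variation to the outcome that the intervention is not aimed at, and they make English and Setswana totals measure different things. The protocol describes all its instruments as standard, with proven validity (Reliability, validity and objectivity of the data collection instruments). An item whose meaning has changed in translation cannot rely on that.

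**Working it through.** **Wording.** Translations are literal and need a Setswana speaker to confirm them.

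| Place | Whose drinking is named |
|---|---|
| English introduction: "now I would like to ask you some questions about your use of alcohol beverages during the past 3 months" | the respondent's |
| Setswana introduction: "dipotso tse di latelang ka tiriso ya nnotagi mo dikgweding tse thataro tse di fetileng" (use of alcohol in the past six months) | none named in this clause |
| English item 9 | the respondent's |
| Setswana item 9, ending *ka ntlha ya nnotagi* (because of alcohol) | none named |
| Setswana items 5 and 10 | the respondent's |

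The possessive was therefore available in the language and used on the same form. Two other features are not part of this point. The sense of 'ever' is no departure, because the English stem has no time limit either. The different look-back periods in the two versions are a separate matter.

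**Effect on eligibility.** Let T be the total when item 9 is correctly scored 0, and d the points wrongly added (2 or 4). Let L be the lower limit: 8 for men, 7 for women.

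- Wrongly included: T < L and L ≤ T + d ≤ 19, so T runs from L − d to L − 1.
- Wrongly excluded at the top: L ≤ T ≤ 19 and T + d ≥ 20, so T runs from 20 − d to 19.

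| | d = 2 | d = 4 |
|---|---|---|
| Men wrongly included | T = 6 to 7 | T = 4 to 7 |
| Women wrongly included | T = 5 to 6 | T = 3 to 6 |
| Either sex wrongly excluded | T = 18 to 19 | T = 16 to 19 |

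**Two cases under the form's own rules.**
- A woman who drinks 2 to 3 times a week, 1 or 2 drinks, and never four or more on one occasion scores 3 + 0 + 0. Items 2 and 3 sum to 0, so she skips to items 9 and 10. With 4 on item 9 and 0 on item 10 her total is 3 + 4 = 7, and she is eligible. Her drinking is within the limits in the protocol's own health education leaflet.
- A man who drinks 4 or more times a week, 1 or 2 drinks, and never five or more scores 4 + 0 + 0. With 4 on item 9 his total is 4 + 4 = 8, and he is eligible.

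**Abstainers.** A 'never' on item 1 also leads to items 9 and 10. Item 9 alone then gives at most 4, below both 7 and 8, so it cannot admit an abstainer by itself.

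**Average size.** If shares a and b of Setswana respondents wrongly score 2 and 4, the mean Setswana score rises by 2a + 4b. The protocol gives neither share, nor the split between languages.

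**The case against.** There are good grounds for doubting that the misreading is common:
- The Setswana health education leaflet uses the same phrase, *ka ntlha ya nnotagi*, where the reader's own drinking is evidently meant.
- Item 7 of the Setswana form also omits the possessive without changing whose drinking is in question.
- The verb in item 9 appears to be in the second person, which would centre the question on the respondent. This too needs a Setswana speaker.
- The Setswana introduction opens by referring to the patient's own life, and item 9 stands among items about the respondent's drinking.
- This is the interview version, so the interviewer can clarify.

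These points make the misreading possible rather than certain. They do not restore equivalence with the English item, since the form prints no clarifying prompt.

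A reader might also infer three stronger things that the documents do not support.

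The first is bias between arms. Patients are randomised, the item is the same in both arms, and the follow-up assessor is to be blinded. The documents give no reason to expect the error to differ by arm.

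The second is a definite loss of treatment contrast. The protocol gives no rate of such answers, no language split and no standard deviation for the AUDIT. The planned analysis tests a treatment-by-time interaction, and a false yes that scores the same at every visit cancels from within-person change. Any dilution percentage would be guesswork. The sample size rests on ART adherence and is not touched.

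The third is that points which stay when the patient drinks less are peculiar to the Setswana form. The English item also keeps 2 points for an injury outside the window.

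**Conclusion.** The concern holds as a translation defect in a scored item. Setswana item 9 omits the restriction to the respondent's own drinking, and so can add 2 or 4 of the 40 points in an unknown share of Setswana interviews. The affected totals are those tabulated above: just below the entry limit, and from 16 to 19 at the top. The consequences are misclassification at entry, noise in the alcohol score and English and Setswana totals that are not strictly comparable. The error is expected to be alike in both arms. This rests on the literal reading of the Setswana text and on some patients taking item 9 as printed. It is worth correcting because wrong inclusions and exclusions cannot be undone once screening has begun.

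**What to change.** Reword Setswana item 9 so that it names the respondent's own drinking, as item 10 of the same form does, for example by ending it *ka ntlha ya go nwa nnotagi ga gago*. Have a Setswana speaker confirm it by back-translation against the English item before the forms are printed, and use the corrected item at baseline, 3 and 12 months. The cost is a few words on one form. The questionnaire pre-test is already scheduled for August 2011, before recruitment starts in September (Time line and research activity), and has its own line of R 1,000 (Budget).
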